## **Amended Protocol**

**Amended on 12/2/2021, Prior to any enrollment of presented study data – This was done after and in response to a pilot test of the original protocol.**

#### **Research Plan**

Objective: To determine the effectiveness of Sani24 in the “real world” hospital environment compared to routine disinfection.

Hypothesis: Daily application of Sani24 will lead to decreased environmental bioburden compared to routine daily disinfection.

Methods:

Design: randomized controlled trial

Outcomes:

- Primary outcome – Total Colony Forming Units (CFUs) on high touch surfaces in acute care hospital rooms over a 24-hour period
- Secondary outcomes
  - o Change in CFU from baseline to 24 hours later
  - o Total CFUs of epidemiologically important vegetative bacteria (MRSA, MSSA, VRE, MDR GN)
    - Proportion of samples with epidemiologically important vegetative bacteria
  - o Change in CFU of epidemiologically important vegetative bacteria from baseline to 24 hours later
    - Change in proportion of samples with epidemiologically important vegetative bacteria
- Descriptive outcome – Patient perception of routine daily disinfection and intervention-disinfectant usage.

Approach:

- Inclusion criteria: Rooms with occupants on contact precautions
- Randomization: High touch surfaces will be randomized by right and left sides, 1:1 to intervention or control.
  - o Following collection of baseline samples:
    - Intervention – team will apply Sani24 to high touch surfaces throughout room on day 0
    - Control – no change in routine daily disinfection
- Routine disinfection tracking
  - o UV-C fluorescing gel dots will be applied to all randomized surfaces to ensure study disinfectant has not been removed from the surface
- Microbiological sampling:
  - o Location:
    - 3 samples will be obtained for each study arm, one at each point of measurement: bedrails, overbed table, and sink

- Timing:
  - Day 0 - immediately before application of disinfectant (intervention) or similar time point (control)
  - Day 1 – 24 hours following the application of disinfectant (intervention) or similar time point (control)
- Measurement:
  - CFUs on high touch objects obtained via sponge and stomacher technique
- Patients will be asked a short series of questions on day 1 about routine daily disinfection and the disinfectant if in the intervention arm
  - Question examples:
    - “How well do you think your room is cleaned?”
    - “How well do you think your room is disinfected?”
    - “Do you have any concerns about the disinfectant being used?”

Study size: 50 patient rooms will be enrolled

- Each measured twice in three locations = 600 sponge samples

[figure not shown]

**Figure 1.** Study design.

Analysis:

Primary and secondary outcomes will be analyzed using a top-down approach.

Primary outcome – Total CFUs on high touch surfaces 24 hours after enrollment

- Total room CFU on day 1 for the entire study
- Total room CFU on day 1 compared between study arms
- Total room CFU on day 1 compared within each couplet
- Sample area CFU on day 1 for the entire study
- Sample area CFU on day 1 compared between study arms
- Sample area CFU on day 1 compared within each couplet

CFU comparisons will be analyzed using the Wilcoxon rank sum test, proportions with the proportion Z score test and categorical variables with the Chi-squared test. A p-value of 0.05 will be considered significant and all statistical tests will be 2-tailed. All testing will be completed using R software (R Foundation for Statistical Computing, Vienna, Austria).

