### State the objectives of the research/project:

To determine the effectiveness of an enhanced strategy for daily disinfection in acute care hospital rooms comparing the addition of sani24 to routine daily cleaning versus the control of routine daily cleaning. We will evaluate the effectiveness of a) adding sani24 to the standard daily cleaning and b) routine daily disinfection in acute care hospital rooms to measure the reduction in bioburden. In other words, we aim to answer the following research question: does the addition of an additional disinfection technology (Sani24) decrease the environmental bioburden in inpatient hospital compared to routine disinfection?

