### Briefly describe research/project activities occurring at Duke, including the source of all data /samples:

- Do not copy and paste an external entity's summary. Please limit to 3 paragraphs.

**Design** – randomized controlled trial.

**Setting** – we will perform this study in the acute care floors of the Duke University Health System:

**Study arms** – This trial will include two study arms:

1. Control – routine, standard disinfection strategies will be used throughout the study.
2. Active Study Arm 1 – Sani24 will be sprayed on three standard high touch areas by study staff at the same point each morning in addition to routine daily disinfection.

**Intervention** – Two acute care patient rooms in similar units will be chosen that meet the following criteria:

1. Rooms from which a patient on contact precautions was discharged.
2. Rooms housing **recently admitted** patients with a projected length of stay  $\geq 3$  days.

Chosen similar rooms will be paired into study couplets. One room will be randomized to intervention or control arm and its pair will be assigned the opposite arm. Hospital personnel and patients will be blinded to the study arm.

Those randomized to intervention rooms will receive applications of Sani24 immediately following enrollment and the successive 2-days in addition to routine daily disinfection. Those randomized to control will receive only routine daily disinfection.

**Procedure** – We will obtain environmental cultures from each study couplet’s room immediately following their enrollment on hospital day 0, and on hospital day 3. Environmental cultures will be obtained using the swab and stomacher technique, per CDC protocols. Cultures will be obtained from three locations: Bedrails, the overbed table and the [sink](#).

**Data Collection** – Total colony forming units (CFU) will be calculated from each culture and aggregated for total room CFU. Culture specimens will be evaluated for specific pathogens: *S. aureus* (MRSA or MSSA), *Enterococci* (VRE or VSE), *Acinetobacter* spp., *Pseudomonas* spp., and *Enterobacteriaceae* of interest such as *E. coli* and *Klebsiella* spp.

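### The amended hypothesis concerns daily application and environmental bioburden, but the design observes one application over 24 hours, and its room-level wording conflicts with randomisation by side

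*Protocol*

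**What the plan says.** All the text at issue is in the Amended Protocol, Research Plan.

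- **Hypothesis:** "Daily application of Sani24 will lead to decreased environmental bioburden compared to routine daily disinfection".
- **Approach, Randomization (allocation):** "High touch surfaces will be randomized by right and left sides, 1:1 to intervention or control".
- **Approach, Randomization (intervention):** "team will apply Sani24 to high touch surfaces throughout room on day 0". No later application is described.
- **Approach, Timing:** a baseline sample on day 0 just before application, and one later sample on day 1, "24 hours following the application of disinfectant (intervention) or similar time point (control)".
- **Analysis, primary outcome:** "Total CFUs on high touch surfaces 24 hours after enrollment". The comparisons listed include total room CFU between arms and within each couplet, followed by the same comparisons by sample area.
- **Study size:** 50 patient rooms, each measured twice in three locations, for 600 sponge samples.

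The exempt application that precedes the amendment describes a different schedule: "Those randomized to intervention rooms will receive applications of Sani24 immediately following enrollment and the successive 2-days". It also pairs whole rooms into couplets.

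**The concern.** A hypothesis fixes what a significant p-value is taken to support. This one names a daily regimen and the bioburden of the environment. The design below it gives one application occasion and one outcome reading, and appears to compare two sides within a room.

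Two things are at stake. First, a positive 24-hour result could be read as evidence for repeated daily use, or a null result held against it, although repeated use is never observed. Second, a contrast between two sides of one occupied room need not equal the effect of treating a whole room. The room-level terms in the Analysis invite the whole-room reading. They also leave unclear which quantity the primary between-arm comparison refers to, because under side-level allocation a room has no single arm.

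An analysis plan would not ordinarily repair this, because the hypothesis, the intervention and the unit of allocation are set in the protocol.

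**Working it through.** **1. Schedule: hypothesis against Approach**

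| Element | Amended Research Plan |
|---|---|
| Regimen named in the hypothesis | daily |
| Application occasions described | 1 (day 0) |
| Readings before application | 1 (day 0) |
| Readings after application | 1 (24 hours) |

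With one application and one later reading, the estimable effect is that of one application at 24 hours. An effect of a second or later application, or one lasting beyond 24 hours, cannot be estimated. The baseline reading feeds the secondary change outcomes but does not lengthen the follow-up.

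For context, the exempt application gives 1 + 2 = 3 applications (enrolment and the next two days), with cultures on days 0 and 3. That text precedes the amendment, so the difference is not itself an error. It does suggest that the word *daily* may have been carried over. The mismatch lies within the amended text and does not depend on the comparison.

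**2. Unit: which layout gives 600 samples?**

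Inputs from Study size and Microbiological sampling: 50 rooms, 3 locations per arm, 2 time points, stated total 600.

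Formula: rooms x arms per room x locations x time points.

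- Both arms in each room: 50 x 2 x 3 x 2 = 600. This reproduces the stated total.
- One arm per room: 50 x 1 x 3 x 2 = 300. This does not.
- Fifty couplets of two whole rooms: 100 x 1 x 3 x 2 = 600. This also gives the total, but it needs 100 rooms and the plan states 50.

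With 50 rooms, only the split-room layout gives 600, and it agrees with allocation by right and left side.

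**3. Room-level wording against the split-room layout**

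- If the two sides of a room are in opposite arms, the intervention cannot also be applied to high touch surfaces throughout that room.
- A room total adds treated and untreated sides, so it cannot be compared between arms unless it is redefined as a per-side sum over the three locations.
- *Couplet* is not defined in the amended text. In the exempt application it means two paired rooms.
- The sample-area comparison between arms does fit side-level allocation.

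**The case against.** The strongest reply is that the plan is open about its horizon. Outcomes, Timing and Analysis all state 24 hours. One application read a day later is one full cycle of a once-daily regimen, and the hypothesis claims no cumulative or sustained effect. On that view a single adjective is loose. This stands to the extent that the direction of the hypothesis is tested over one day. A reader might infer that the hypothesis is not tested at all, and the documents do not support that. The reply does not make one cycle informative about repeated use.

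A second reply is that room total could mean the sum over three locations on one side, and couplet the two sides of a room. That is a reasonable reading and may be the intended one, but the amended text does not say so. The study design figure, which might settle it, is not visible here.

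Two further inferences are tempting and should not be drawn:

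- **That no room is ever fully treated.** This follows from side-level allocation, but the same section says the product goes on surfaces throughout the room. It is a contradiction to reconcile and not an established count.
- **That the comparator is stated two ways.** The exempt application asks "does the addition of an additional disinfection technology (Sani24) decrease the environmental bioburden in inpatient hospital compared to routine disinfection", which is one comparison: routine disinfection with Sani24 against routine disinfection alone. The amended text does not contradict this. Its control arm keeps routine disinfection unchanged, and its tracking dots go on all randomised surfaces.

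It is also fair to say that the documents contain no planned conclusion, so overclaiming is a risk and not a stated intention. Any carry-over between sides is a separate validity question, which rewording would not resolve.

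**Conclusion.** The point holds in a limited form. The hypothesis reaches beyond the design in time: one application and one reading at 24 hours support a statement about that day only. In space, side-level allocation and the 600-sample count imply both arms in one room, which conflicts with application throughout the room and with room totals compared between arms and within couplets.

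The size is one application occasion and one post-application reading, with no data on repeated application. No power figure, threshold or test depends on the point. It is still more than clerical, because it changes what a significant result may be said to support and what the room-level primary comparisons mean.

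The conclusion rests on two assumptions: that no application occurs between day 0 and the day 1 sample beyond the one described, and that 50 rooms is the intended number. If 100 paired rooms were intended, the sample count would no longer favour split rooms and the conflict would lie with the randomisation sentence and the stated room number.

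**What to change.** 1. Reconcile the hypothesis with the application schedule in the Approach. Which schedule is right is for the investigators; this review takes no position.
2. Reconcile the statement that Sani24 is applied throughout the room, the room-total comparisons and the term couplet with allocation by right and left side. Define each retained term at the level at which it is analysed.
3. Then word the objective and hypothesis for the contrast delivered. If the Approach stands as written, that is the difference in CFU at 24 hours between treated and untreated sides after one application. Add a sentence that repeated-application and whole-room effects are not estimated.

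The cost is rewording and a narrower claim. If the Approach stands, sampling, sample size and tests need not change on account of this point.

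### The only test named for proportions does not, in its standard form, compare the change in pathogen-positive samples between Sani24 and control

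*Protocol*

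**What the plan says.** In the amended Research Plan, under Outcomes, the outcome "Change in proportion of samples with epidemiologically important vegetative bacteria" is a sub-item of "Change in CFU of epidemiologically important vegetative bacteria from baseline to 24 hours later", so the time frame is day 0 to day 1. The hypothesis is comparative: "Daily application of Sani24 will lead to decreased environmental bioburden compared to routine daily disinfection".

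The Approach section states "High touch surfaces will be randomized by right and left sides, 1:1 to intervention or control". Each room therefore supplies both arms, and bedrails, overbed table and sink are sampled in each arm on both days.

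The Analysis section says that it covers primary and secondary outcomes. It gives one sentence on tests, "CFU comparisons will be analyzed using the Wilcoxon rank sum test, proportions with the proportion Z score test and categorical variables with the Chi-squared test", followed by "A p-value of 0.05 will be considered significant and all statistical tests will be 2-tailed". Comparisons between arms and within couplets are itemised only for day-1 CFU, the primary outcome. No contrast is written for the change in proportion.

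**The concern.** The protocol is not silent on method here. It gives every proportion one test and one significance threshold. In its usual form that test does not yield a Sani24-versus-control result for a change. An arm's change can be negative, so it cannot be entered as a proportion.

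The easiest way to apply the test to a change is day 0 against day 1 within each arm. Two such p-values, one below 0.05 and one above, are not a comparison of arms. Anything that lowers counts on both halves, such as continuing routine disinfection or removal by the baseline sponge, moves both tests, and chance then decides which one crosses the threshold. At stake is a claim of an effect on the clinically important organisms when both halves changed equally.

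**Working it through.** **Sample count.** The inputs are in the Research Plan: "50 patient rooms will be enrolled", two halves, three sites, two days. 50 × 2 × 3 × 2 = 600, which reproduces the protocol's total. Each arm has 50 × 3 = 150 samples per day.

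**What the named test can take.** Write T0, T1 for the Sani24 proportions on day 0 and day 1, and C0, C1 for control. The two-proportion Z is (a − b) / √[p(1 − p) × 2/150], with p the pooled proportion. The between-arm question is D = (T1 − T0) − (C1 − C0). No single pair (a, b) gives D.

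**Illustration with assumed counts out of 150.** Sani24 goes from 60 to 42, control from 60 to 47.

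- Within Sani24: p = 102/300 = 0.340, SE = 0.0547, z = −0.120/0.0547 = −2.19, P = 0.028.
- Within control: p = 107/300 = 0.357, SE = 0.0553, z = −0.0867/0.0553 = −1.57, P = 0.117.
- Difference in changes, unpooled: D = −0.120 + 0.0867 = −0.0333. SE = √[(0.240 + 0.2016 + 0.240 + 0.2152)/150] = 0.0773, z = −0.43, P = 0.67.
- Day 1 between arms: 42 against 47, P = 0.53.

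The within-arm pair suggests an effect; neither direct comparison of arms does.

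**How often this would happen.** The documents give no positivity rates, so all rates below are assumed. The true change is the same in both arms and samples are treated as independent. If q is the chance that one arm's before-after test is significant, the chance that Sani24 is significant and control is not is q(1 − q).

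| Shared change | q | Sani24 only |
|---|---|---|
| 20% to 12% | 0.47 | 0.47 × 0.53 = 0.25 |
| 30% to 20% | 0.52 | 0.52 × 0.48 = 0.25 |
| 40% to 30% | 0.44 | 0.44 × 0.56 = 0.25 |
| 10% to 5% | 0.37 | 0.37 × 0.63 = 0.23 |
| 20% to 10% | 0.69 | 0.69 × 0.31 = 0.21 |
| 20% to 5% | 0.985 | 0.985 × 0.015 = 0.015 |

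With small or no change, the chance of a significant fall in Sani24 only is about 6% (20% to 18%) and about 2.4% (no change). A direct two-sided 0.05 test of D would favour Sani24 in 2.5%. The excess therefore needs a shared fall of moderate size; it peaks at 25%, where q is one half.

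**The difference-in-changes Z.** With independent samples it holds its level: about 5% in simulation. Here the samples are not independent. T0 and T1 come from the same surfaces, and T and C from the same room. Positive correlation within those pairs reduces the variance of D, so the independent formula generally gives too large a standard error. In a simulation with assumed room and surface correlation, this Z rejected in about 2% under no effect and had 31% power. A signed-rank test on per-room differences in change had 5% and 41%. The correlation is assumed, so only the direction should be relied on.

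**The case against.** The strongest case against runs as follows. No before-after test is written anywhere; the hypothesis is comparative, and every comparison itemised in the Analysis section is between arms or within couplets. The form of the Z test is not fixed, and a Z statistic for D uses the same data. The share of samples turning from positive to negative is itself a proportion, and the chi-squared test could take gained, lost or unchanged by arm. The exact contrast for a sub-item of a secondary outcome is usual material for a statistical analysis plan, which is not shown. Day-1 positivity is a separate secondary outcome that the named test can compare between arms.

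Much of this stands. A reader might infer that the protocol prescribes a within-arm test, or that the arms cannot be compared on this outcome by any Z test. The documents support neither. Nor is the 25% an error rate of the stated plan: it depends on a use that the protocol does not instruct and on assumed rates, and it would be smaller if the two halves of a room move together.

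Two things remain. The protocol names a test, so a later plan would have to replace that choice and not merely complete it. And the ways of rescuing it with independent-samples tests disregard pairing within room; the Z for D also disregards repeat sampling of surfaces. The share turning negative, taken alone, ignores sites that become positive.

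**Conclusion.** The point holds as a poorly fitting choice of test for one secondary outcome. The standard two-proportion Z does not compare the change between arms, and the version that does compare it uses a standard error that ignores the design. The first part follows from the form of the test and needs no assumption. The second rests on positive correlation between samples of the same surface and of the same room, which the side-by-side design makes likely but for which the documents give no figure.

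The size is illustrative: about 1.5% to 25% over the assumed shared changes if an arm effect were inferred from within-arm tests, against 2.5% for a direct test. The primary outcome is not affected by this point. The change should be made because the outcome concerns the pathogens of interest and the correction costs almost nothing.

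**What to change.** In the Analysis section, take this outcome out of the general sentence on proportions and give it its own. For each room and half, count positive sites (0 to 3) on day 0 and day 1 and take the change. Subtract the control half's change from the Sani24 half's, giving a difference between −6 and 6 per room, and test these over the 50 rooms with a Wilcoxon signed-rank test. Zeros and ties will be common if positives are sparse, so state how they are handled.

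An alternative is a logistic model of day-1 positivity by arm, conditional on room, with day-0 positivity of the same surface as covariate. Choose one before the data are analysed.

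Add that day 0 to day 1 changes within an arm are descriptive and are not used to infer an arm effect.

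The cost is a sentence or two of text and a few lines of R. No extra rooms or samples are needed.

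### The Sani24 application line is worded for the whole room, but the randomised unit is one side of a room, and no sentence shown confines application to the intervention side

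*Protocol*

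**What the plan says.** Everything relevant is current text in the Amended Protocol, Research Plan.

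- Unit of randomisation (Approach, Randomization): "High touch surfaces will be randomized by right and left sides, 1:1 to intervention or control".
- Intervention, nested under that bullet: "team will apply Sani24 to high touch surfaces throughout room on day 0".
- Control, the next line: "no change in routine daily disinfection".
- Sampling (Approach, Microbiological sampling): "3 samples will be obtained for each study arm, one at each point of measurement: bedrails, overbed table, and sink".
- Size (Study size): "50 patient rooms will be enrolled", followed by "Each measured twice in three locations = 600 sponge samples".

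The sampling times are tied to the application of disinfectant for intervention and to a comparable moment for control.

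The exempt application that precedes the amendment describes a different, superseded design with paired rooms: "One room will be randomized to intervention or control arm and its pair will be assigned the opposite arm". The difference between the two designs is not an error. It matters here only because it suggests where the room-wide wording may have come from.

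**The concern.** With one arm per room, an instruction to treat surfaces all over the room is unproblematic, because the control surfaces are elsewhere. With sides randomised within a room, the control surfaces are a short distance from the treated ones, in the same room and sometimes on the same piece of furniture. The area to which the product is applied then defines the treatment contrast. The one sentence that describes this area names the room and not the side.

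The primary outcome is total CFU 24 hours after application, compared between arms. It depends on the control-side surfaces receiving routine disinfection only. If some of them receive Sani24, the comparison understates any effect of the product, and nothing in the day 1 counts would reveal it.

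**Working it through.** **1. Do both arms lie in every room?** The inputs are 50 rooms, 3 locations, 2 time points and 600 samples, all from the Research Plan (Study size and Microbiological sampling).

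Samples = rooms x arms per room x locations x time points.

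- Two arms per room: 50 x 2 x 3 x 2 = 600. This reproduces the stated total.
- One arm per room: 50 x 1 x 3 x 2 = 300. This does not, and 600 samples would need 600 / (3 x 2) = 100 rooms.

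The count therefore agrees with the randomisation line: the control surfaces are the other side of the same room.

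**2. Can the intervention and control lines be carried out together?** There are two readings.

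- Literal: high touch surfaces all over the room receive Sani24. The control side is among them, so its care does change, and the control line is breached.
- Contextual: the label on the line and the bullet above it limit the instruction to surfaces allocated to intervention, and the reference to the room means at each location. Both lines can then be followed.

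The text shown does not settle which is meant. Some nearby wording also has a room-level flavour. Patients are asked about the disinfectant only if they belong to the intervention arm, although under side randomisation every room holds both arms. The analysis list compares total room CFU between arms. Other wording points to the sides: the sample count, the sampling of each arm at three locations, and the timing lines.

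**3. What would treatment of the control side do to the comparison?** Day 1 gives 50 x 3 = 150 samples per arm. Let s be the share of control-side surfaces that receive Sani24, and d the true difference in mean (on whatever scale is used) between treated and untreated surfaces. Assume that the product acts equally on both sides. The expected difference between arms is then

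d - s x d = d x (1 - s).

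The document gives no value for s, so a range is shown:

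| s (assumed) | control-side day 1 samples from treated surfaces | share of d retained |
|---|---|---|
| 0 | 0 of 150 | 100% |
| 0.2 | 30 of 150 | 80% |
| 0.5 | 75 of 150 | 50% |
| 1 (literal reading followed in full) | 150 of 150 | 0% |

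The direction is always toward no difference. The table shows dilution only. It is not a forecast of what happened in the rooms.

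**4. Can this be turned into power?** No. The protocol states no effect size, standard deviation or left-right correlation, and no power calculation that could be reproduced. It names the Wilcoxon rank sum test, which is unpaired, for data in which each room supplies both arms. A power figure would rest on assumed inputs throughout.

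**The case against.** The strongest reply is that the line should be read in its place. It carries the label for the intervention arm and sits under a bullet whose randomised object is a side. The control line and both timing lines presuppose that control surfaces get no application. Treating both sides would make the randomisation pointless, and the people applying the product are the study team, working from a plan amended after a pilot test. Figure 1, which shows the study design, is not available here and may depict the left-right split.

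Most of this stands. A workable reading exists, and it is probably the intended one. What remains is that the only sentence on where the product goes names the room, and that no available sentence limits it to a side. A figure could support the narrower reading, but it would not remove contrary wording from the text.

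A reader might infer two stronger conclusions, and the documents support neither. The first is that the two instructions are irreconcilable and the contrast is lost. That follows only on the literal reading, and nothing shows that control sides were treated. The second is a specific loss of power, for instance from a paired calculation with an assumed effect, or the statement that power would fall to exactly the 5% level. The named test is unpaired. With positively correlated sides, its rejection rate under no difference would not be 5% but lower. The inputs are also not in the document.

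**Conclusion.** The point holds as an ambiguity in a sentence that defines the treatment contrast, and it should be fixed. The randomised unit is a side within a room, as the 600-sample count confirms, while the application line is worded for the room.

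The size is conditional. The expected difference shrinks by the share of control-side surfaces treated, from no loss on the contextual reading to a complete loss if the literal wording were followed in every room. This assumes equal action of the product on both sides. No figure for power follows from the document. Confidence in the wording conflict is high. Confidence that it would mislead staff is moderate, given the label, the control line and the figure that is not shown.

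**What to change.** Reconcile the application line with the unit of randomisation. Which of the two is intended is for the sponsor to state.

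- If sides are randomised, say that application is confined to the surfaces on the side allocated to intervention and that the opposite side receives none. The count of 600 is unaffected: 300 samples per arm, 150 of them on day 1.
- If whole rooms are to be treated, the room must be the randomised unit, and the sample count and analysis must be rewritten to match. With 50 rooms and the same sampling, the count would be 300 unless sampling or the number of rooms changes.

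In either case, align the lines on patient questions and total room CFU with the chosen unit.

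The first option costs one sentence. Recording which side was sprayed, for each surface, is an optional addition of one field on the room form. It would let the team show that the contrast was kept, but its absence from this short plan is not an error.

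### Day-0 CFU is cultured on every randomised surface, but the primary day-1 comparison leaves it out: an avoidable loss of efficiency, not a bias

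*Protocol*

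**What the plan says.** All references are to the Research Plan in the Amended Protocol.

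- **Allocation (Approach):** "High touch surfaces will be randomized by right and left sides, 1:1 to intervention or control". Each of the 50 rooms therefore holds both arms.
- **Sampling (Approach):** "3 samples will be obtained for each study arm, one at each point of measurement: bedrails, overbed table, and sink". The day-0 sample is taken "immediately before application of disinfectant (intervention) or similar time point (control"), and the day-1 sample 24 hours later. The stated total is 600 sponges.
- **Primary outcome (Analysis):** "Total CFUs on high touch surfaces 24 hours after enrollment". Six analyses follow: room totals and sample-area counts, each for the whole study, between arms and within couplets. All six are on day-1 CFU, for example "Total room CFU on day 1 compared between study arms".
- **Test (Analysis):** "CFU comparisons will be analyzed using the Wilcoxon rank sum test", and "A p-value of 0.05 will be considered significant and all statistical tests will be 2-tailed".
- **Use of baseline (Outcomes):** "Change in CFU from baseline to 24 hours later" is a secondary outcome, repeated for the epidemiologically important bacteria as a change in CFU and in proportion positive. No adjustment or transformation is stated.

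**The concern.** A pre-treatment measurement of the outcome, on the same surfaces and by the same method, is usually the best available predictor of the follow-up value. Here it is collected at the cost of half the laboratory work and then kept out of the primary comparison. Contamination that persists from day 0 to day 1 and differs between the two sides of a room stays in the primary comparison as noise.

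The change outcome does not make up for this. Subtracting baseline fixes its coefficient at 1, whatever the data say. When persistence is weak, subtraction adds more noise than it removes. With 50 rooms and no power statement in the protocol, efficiency deserves attention.

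**Working it through.** **Step 1. The protocol's own count.** 50 rooms x 2 sides x 3 sites x 2 times = 600, which reproduces the stated total. The day-0 share is 50 x 2 x 3 = 300. One set of three sites per room would give only 50 x 3 x 2 = 300 in all, so the 600 requires both sides to be sampled at both times.

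**Step 2. Variances.** Let D0 and D1 be the within-room differences (intervention minus control side) in log CFU on day 0 and day 1, with equal variance (assumed) and correlation r. Relative to the variance of D1 alone:

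- adjusted for D0: 1 - r^2
- change, D1 - D0: 2(1 - r)

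The gap is 2(1 - r) - (1 - r^2) = (1 - r)^2, so change is less precise than adjustment at every r below 1. Change is less precise than day 1 alone when 2(1 - r) > 1, that is, when r < 0.5.

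**Step 3. Power.** The documents give no effect size, SD or r. Assumed: 50 pairs, true difference 0.4 SD of D1, two-sided alpha 0.05. The non-centrality is 0.4 x sqrt(50) = 2.83 for the paired day-1 t test, which gives 79%. For the other two analyses, divide 2.83 by the square root of the relative variance. The adjusted figures also allow for estimating the slope.

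| r | 1 - r^2 | 2(1 - r) | Paired day 1 | Adjusted | Change | Rooms for equal precision, 50(1 - r^2) |
|---|---|---|---|---|---|---|
| 0 | 1.00 | 2.0 | 79% | 78% | 50% | 50 |
| 0.2 | 0.96 | 1.6 | 79% | 80% | 59% | 48 |
| 0.3 | 0.91 | 1.4 | 79% | 82% | 65% | 45.5 |
| 0.5 | 0.75 | 1.0 | 79% | 89% | 79% | 37.5 |
| 0.7 | 0.51 | 0.6 | 79% | 97% | 94-95% | 25.5 |

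**Step 4. The tests the protocol names.** The comparator in step 3 is paired; the planned rank sum test is not. Simulation separates the two effects. It used 50 rooms, 3,000 trials per scenario, lognormal counts, and an effect of 0.56 SD of a single side's log count, which gives 80% power for an unpaired comparison of independent sides. The variance shares are assumed.

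| Room share / persistent side share | Rank sum, day 1 | Rank sum, raw change | Signed-rank, day 1 | Paired plus baseline |
|---|---|---|---|---|
| 0.3 / 0.2 | 81% | 52% | 89% | 93% |
| 0.5 / 0 | 86% | 52% | 97% | 97% |

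In the first row r = 0.2/(0.2 + 0.5) = 0.29; in the second r = 0. Pairing gives most of the gain. Baseline adds 3 to 4 points when side differences persist and about 1 point or less when they do not. Across the six scenarios run, rank sum on raw change had 33% to 61% power, against 77% to 86% for rank sum on day 1.

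**The case against.** **It is not an error.** Sides are randomised, and chance baseline differences are part of the sampling variation that the test already allows for. Using day-0 cultures for named secondary outcomes contradicts nothing in the protocol. This stands in full. A reader might infer that the primary result is biased by baseline imbalance; the design does not support that.

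**The gain may be small.** The relevant r is what remains after the shared room effect is removed, and it has to survive a day of patient contact and routine cleaning. At r of 0 to 0.2 adjustment changes almost nothing. This also stands. A reader might infer that substantial power is certainly being lost, but no figure in the protocol shows it.

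**Most of the practical loss comes from the unpaired test.** This is right in the scenarios of step 4. The within-couplet comparisons do not remove that problem, because the only test named for CFU is the rank sum. Pairing is a separate issue; the step 3 gains are measured over a paired test and do not include it.

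**Raw CFU change is dominated by a few very high counts.** A reader might infer this too, but a rank test bounds the influence of each value. The case against the change score is the variance argument and the simulated power.

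**The choice could be left to the analysis plan.** This does not stand. The protocol itself fixes the contrast, the test and the significance level, and a plan that adjusted for baseline would depart from that text.

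**Conclusion.** The point holds as a matter of efficiency. Half of the cultures are baseline measurements that the primary comparison does not use, and the only planned use, an unadjusted change, is less precise than adjustment at every r below 1 under equal variances. The primary comparison remains unbiased.

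The size cannot be taken from the documents. It ranges from nothing (about one point of power lost) at r = 0, through about 3 points at r = 0.3, to about 10 points at r = 0.5 and 18 at r = 0.7, all over a paired day-1 test with 79% power. These figures rest on the assumed 0.4 SD effect, equal variances on the two days and normal log differences. This is a worthwhile, cheap improvement and no ground for doubting the validity of the trial.

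**What to change.** Replace the primary test with one sentence to this effect: for each room, take the intervention-minus-control-side difference in log10(total CFU + 1) on day 1 and regress it on the same difference on day 0; the intercept is the treatment effect, back-transformed to a ratio of geometric means of CFU+1 with a 95% CI.

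If a mixed model is preferred, include fixed room effects or separate within-room and between-room baseline terms. A random-intercept model with a single baseline term is not equivalent, because it blends the two slopes. In 60 simulated trials with a persistent room effect, its baseline slope averaged 0.64 against a within-room slope of 0.13, and the treatment estimates differed.

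Keep the within-room signed-rank test on day-1 CFU as a sensitivity analysis, and report change from baseline descriptively.

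No new data are needed, and the same sentence also resolves the unpaired test. The cost is that a log-scale model, with 1 added for zero counts, replaces a purely rank-based primary test. One degree of freedom is spent, with negligible loss of power if r is near 0.
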